### Sample Size Determination

The following formula for comparing 2 groups [17] was used for the calculation of the minimum sample size (n):

 where *z*_α/2_ = *z*_0.15/2_ = 1.44 (from *z* score table), Zβ/2 = z_0.15/2_ = 0.75 (from *z* score table at 75%), P_1_= 0.32, P_2_ = 0.22, P_1_–P_2_ = pooled prevalence (prevalence in intervention group [P1] + prevalence in control group [P2]/2):

Considering the 10% nonresponse rate, the sample size (n) was adjusted to 242.

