**Methods:**

A two-arm cluster randomized controlled trial will be conducted in the Foumban Health District and Galim Health District. The intervention and control arms will each comprise 5 clusters with 121 child–caregiver pairs. Participants in the intervention arm will be organized into 5 caregivers’ peer-support platforms. A total of 12 educational sessions will be assigned to the intervention group by trained female Mbororo nutrition volunteers (n=6) and community health workers (n=6). The control arm will receive routine facility-based nutrition education. Data will be collected at 3-month and 6-month follow-up. Both descriptive statistics and multivariate logistic models will be used to estimate the effect of culturally tailored community-based nutrition education intervention (independent variable) on outcome variables (caregivers’ knowledge, attitude, and practice), child growth (weight, height/length, weight for age), and morbidity status (diarrhea, cough, and fever) between both arms. Data assessors will be blinded to the group allocation. Ethical approval (reference no. 2019/1002-07/UB/SG/IRB/FHS) was obtained from the Faculty of Health Sciences Institutional Review Board at the University of Buea.

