### Trial Design

As presented in Figure 1, this is a 2-arm parallel intervention study designed as a cluster randomized controlled trial. The randomization units will be clusters to prevent contamination between the experimental and control arms. A computer-generated list of 10 randomly selected clusters will be produced and placed in sealed, opaque envelopes.

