**Figure 1 figure1:**
[figure not shown]
Flow chart showing cluster randomization and follow-up for the nutrition, water, sanitation, and hygiene (Nu-Wash) model.

The clusters will be allocated in a 1:1 ratio in both arms. The study will be single blinded, as only the data assessors (data collectors and analysts) will be blinded to the group allocations. Within each cluster, children and caregivers meeting the inclusion criteria will be recruited for the study. Informed consent and assent will be obtained from caregivers before the intervention. Caregivers in the experimental arm will receive nutritional education under the nutrition, water, sanitation, and hygiene (Nu-WASH) model, and caregivers in the control arm will be exposed to routine nutrition education offered by health staff in the study area. Data will be collected at 3-month and 6-month follow-up.

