#### Step 2: Formation of CPGs

Caregivers in the intervention arm (n=121) were organized into 5 peer-support groups of 20 to 30 members. Each group per cluster will serve as the platform for group sessions and for interactions to enhance learning.

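### The stated minimum of 242 pairs has no allowance for clustering, although the trial randomises only 10 communities; the loss is modest at an ICC of 0.01 and large at 0.05 and above

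*Protocol article*

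**What the plan says.** On the design, the Trial Design section is explicit: "The randomization units will be clusters to prevent contamination between the experimental and control arms". The abstract's Methods paragraph gives the scale: "The intervention and control arms will each comprise 5 clusters with 121 child–caregiver pairs". In the intervention arm each cluster is also the unit of delivery. According to Step 2 (Formation of CPGs), caregivers "were organized into 5 peer-support groups of 20 to 30 members", one group per cluster, and Step 4 gives each group two facilitators and 12 shared sessions.

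On the sample size, the section reports that a "formula for comparing 2 groups [17] was used for the calculation of the minimum sample size (n"). The inputs it lists are:

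- z = 1.44, for a two-sided alpha of 0.15;
- a power term of "0.75 (from *z* score table at 75"%);
- the prevalences "P_1_= 0.32, P_2_ = 0.22";
- a pooled prevalence.

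It then applies 10% nonresponse and arrives at 242. The Data Analysis Plan sets significance at 0.05 and says that the analysis will take clustering into account. Table 1 makes the primary outcomes continuous changes in knowledge, attitude and practice (KAP) scores.

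**The concern.** A two-group formula for proportions counts every pair as an independent observation. Pairs from the same community resemble one another, and intervention pairs also share a peer group, its facilitators and its sessions. The between-arm comparison rests on 10 communities, which leaves 10 − 2 = 8 degrees of freedom. A sample size without an ICC, a cluster size or a cluster count therefore overstates the information in 242 pairs, and it never examines the number of clusters, which is the quantity that limits this design. At stake is how the result is read. If 242 is presented as the required minimum, a null result may be taken as evidence of no effect when the trial could reliably detect only fairly large differences.

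**Working it through.** **Inputs.** From the protocol article: 5 clusters and 121 pairs per arm, so m = 121/5 = 24.2; P1 = 0.32 and P2 = 0.22; z values 1.44 and 0.75; 10% nonresponse; analysis alpha 0.05. Assumed, because the article gives no value: ICC of 0.01, 0.02, 0.05 and 0.10, and equal cluster sizes.

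**1. The plan's own figure.** (1.44 + 0.75)² = 4.7961.

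- Pooled variance: 4.7961 × 2 × 0.27 × 0.73 / 0.10² = 189 per arm.
- Unpooled variance: 4.7961 × (0.2176 + 0.1716) / 0.10² = 187 per arm.

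The total is about 373 to 378 before nonresponse and 411 to 420 after it, so 242 does not follow from the printed inputs. The nearest route found takes z = 0.674 (the value for 75% power) and reads the pooled prevalence literally as 0.32 + 0.22/2 = 0.43. Then (1.44 + 0.674)² × 2 × 0.43 × 0.57 / 0.10² = 219.1, rounded up to 220, and 220 × 1.10 = 242. This route is conjecture, and it uses a per-arm number as the total. On it, nonresponse explains the whole final step and no room is left for a design effect.

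**2. Information.** Design effect DE = 1 + (24.2 − 1) × ICC; effective pairs per arm = 121/DE; loss = 1 − 1/DE.

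**3. Power for 32% versus 22%.** SE = √[(0.2176 + 0.1716) × DE / 121]; noncentrality = 0.10/SE; two-sided noncentral t on 8 df (critical values 1.592 at alpha 0.15 and 2.306 at alpha 0.05).

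**4. Detectable score difference at 80% power, alpha 0.05.** (2.306 + 0.889) × √(2 × DE / n) in SD units, with n = 121. After 10% loss, n = 108.9 and m = 21.8.

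| ICC (assumed) | DE | Effective pairs per arm | Loss | Power, alpha 0.15 | Power, alpha 0.05 | Detectable SD | Detectable SD after 10% loss |
|---|---|---|---|---|---|---|---|
| 0.01 | 1.23 | 98 | 19% | 52% | 29% | 0.46 | 0.48 |
| 0.02 | 1.46 | 83 | 32% | 47% | 25% | 0.50 | 0.52 |
| 0.05 | 2.16 | 56 | 54% | 38% | 19% | 0.60 | 0.62 |
| 0.10 | 3.32 | 36 | 70% | 31% | 14% | 0.75 | 0.76 |

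**5. Reference without clustering.** With 242 independent pairs (normal approximation), power is about 63% at alpha 0.15 and about 42% at alpha 0.05. With ICC = 0 but 8 df, these become 58% and 34%. The detectable difference for independent pairs is 0.36 SD.

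**6. Limit set by the clusters.** With 5 clusters per arm, the effective number per arm cannot exceed 5/ICC: 100 at an ICC of 0.05 and 50 at 0.10. Above an ICC of 5/189 ≈ 0.026, adding pairs in the same communities could not reach even the 189 per arm that the printed inputs require.

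**The case against.** Several points can fairly be made for the plan.

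- The equation and its worked line are absent from the text available, so a clustering term cannot be ruled out by inspection. This stands as a limit. However, the surviving list of symbols has no such term, and nonresponse is the only adjustment named.
- The article is not blind to clustering. A reader might infer that the analysis will ignore it; the Data Analysis Plan says the opposite. But a correct analysis does not repair the stated size. It makes the lost precision visible.
- A reader might put the whole of the 29% to 14% power down to clustering. The figures do not support that. Power is already about 42% at alpha 0.05 with independent pairs, because the trial was sized at 0.15 and will be tested at 0.05. Like for like at 0.15, the fall is from about 63% to between 52% and 31%, part of it from the 8 df.
- A reader might conclude that 242 pairs carry far less information whatever the ICC. At 0.01 the loss is 19%, so that description fits only from about 0.05 upwards, and the article gives no ICC with which to choose.
- Power for two proportions says little about continuous KAP scores. This is correct, and it is why the fix is stated in SD units.

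**Conclusion.** The point holds. The sample size as described makes no allowance for randomising 10 communities, and 242 cannot stand as the minimum for this design. The size of the loss is conditional on the ICC: 19% of the information at 0.01, and 54% to 70% at 0.05 to 0.10. The 8 df lower power further at any ICC. The conclusion rests on the listed symbols being complete, on equal clusters of 24.2, and on assumed ICCs. It does not follow that inserting a design effect would by itself put the section right: 242 fails to reproduce from the printed inputs even without clustering, the alpha differs between sizing and analysis, and the calculation addresses a prevalence rather than the primary score outcomes.

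**What to change.** Remove the statement that 242 is the minimum required sample, and report the number of clusters and pairs as fixed. In its place, give the minimum detectable difference in each KAP change score for 5 clusters per arm, using 1 + (m − 1) × ICC and t critical values on 8 df at alpha 0.05, over a stated range of ICCs. Say that the SD is that of the change score. Over ICCs of 0.01 to 0.10 the result is about 0.46 to 0.75 SD at 80% power, or 0.48 to 0.76 SD after 10% loss.

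The baseline KAP data already collected can inform the ICC range but should not replace it. An ICC estimated from 10 communities is imprecise, the ICC of a change score may differ from that of a baseline score, and the group sessions may raise it in the intervention arm.

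The cost is a short calculation and one rewritten paragraph, with no added enrolment. The stated precision becomes less favourable.

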### Data Analysis Plan

Like the procedure at baseline, 1 biostatistician and 2 trained data entry clerks will be responsible for the endline data management and analysis. Data will be cross-checked for inconsistencies (outliers and extreme points) and errors and incompleteness before, during, and after manual entry into SPSS version 23 (IBM Corp). The data will be further treated for reverse coding, potential points, and outliers, as well as missing data, before being exported to SmartPLS2 for further investigation and fitting of the structural model.

Sociodemographic and child morbidity data will be analyzed and summarized using descriptive statistics. The data will be expressed as mean (SD) or median (range) for continuous variables and as a number (percentages) for categorical variables. The *t* test and analysis of variance for comparing group means will be used for primary and secondary outcome variables. A chi-square test will be applied to analyze the categorized variables. Child nutrition outcomes will be computed from anthropometric indices using Stata version 11 (StataCorp) and compared with the WHO 2006 growth standard median [20].

Results for group comparisons will be expressed as a risk ratio for binary outcomes, corresponding to 2-sided 95% CIs, and associated *P* values. *P* values will be adjusted to 2 decimal places with values less than .01 reported as <.01. Adjusted analyses using baseline variables will be performed using multivariate logistic regression to determine the continuing influence of key baseline characteristics on the outcomes. The Kaplan-Meier survival analysis will be used for timed variables like morbidity. Intention-to-treat analysis will be used, and the clustering effect will be considered in the analysis. All analyses will be performed at a 95% CI. The significance level will be set at a *P* value <.05.

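### The sample size was calculated at a two-sided 15% significance level, but results will be judged at P<.05; at 5%, 121 pairs per arm give about 42% power for 32% v 22%, not about 62%

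*Protocol article*

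**What the plan says.** The Sample Size Determination section gives these inputs:

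- Significance term: "where *z*_α/2_ = *z*_0.15/2_ = 1.44 (from *z* score table".
- Power term: "Zβ/2 = z_0.15/2_ = 0.75 (from *z* score table at 75" per cent.
- Proportions: "P_1_= 0.32, P_2_ = 0.22", with a pooled value described as their average.
- Result: "Considering the 10% nonresponse rate, the sample size (n) was adjusted to 242".

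The Abstract (Methods) and the Results section use 242 as the total, with 121 child–caregiver pairs and 5 clusters in each arm.

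The Data Analysis Plan sets a different level for the tests. Group comparisons of binary outcomes are to be given as risk ratios "corresponding to 2-sided 95% CIs, and associated *P* values". For the analyses as a whole it says "All analyses will be performed at a 95% CI" and then "The significance level will be set at a *P* value <.05".

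No section explains the 15% level or links it to the 5% rule.

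**The concern.** The significance level in a sample-size calculation should be the one at which the result will be judged. Here the calculation uses 1.44 and the decision rule implies 1.96. The 1.44 does not look like a slip in one digit, because the subscript (0.15/2) and the value agree. Read one-sided, it would be a 7.5% level, which is not 5% either.

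At stake is how a null result will be read. The article presents 242 as an adequate minimum. If power at the threshold in use is well below what the calculation implies, a real effect of the assumed size could easily be missed and then reported as the intervention not working. Moving the decision rule to 15% would remove the mismatch only by tripling the false-positive rate that the Data Analysis Plan sets.

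**Working it through.** **Inputs.** From Sample Size Determination: z for significance 1.44, z for power 0.75, P1 = 0.32, P2 = 0.22, nonresponse 10%. From the Abstract: 121 pairs per arm. From the Data Analysis Plan: two-sided 5%, so z = 1.96. Assumed, because the formula is not visible: n per arm = 2 × p(1 − p) × (z_a + z_b)² / (P1 − P2)², with p = (0.32 + 0.22)/2 = 0.27. All steps treat caregivers as independent.

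**1. Which level is 1.44?** z(1 − 0.15/2) = 1.4395, so 1.44 is two-sided 15%. The two-sided 5% value is z(0.975) = 1.960.

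**2. Can 242 be reproduced?** 2 × 0.27 × 0.73 = 0.3942.

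- Stated z values: 0.3942 × (1.44 + 0.75)² / 0.10² = 189 per arm, or 378 in total.
- With 10% nonresponse: 189.1 × 1.1 = 208 or 189.1/0.9 = 210 per arm, which is 416 to 420 in total.
- With a continuity correction: 209 per arm, or 229 to 232 after nonresponse.

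None of these gives 242, as a total or per arm. A power term of 1.036 (85% power) gives 241.8 per arm before nonresponse. That may be coincidence, and it conflicts with both the stated 0.75 and the use of 242 as a total.

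**3. Power of the trial as sized, for 32% v 22%.** Power = Φ(0.10/SE − z_a), with SE = √(0.3942/n).

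| Pairs per arm | SE | 0.10/SE | Power at 15% | Power at 5% |
|---|---|---|---|---|
| 121 | 0.0571 | 1.752 | Φ(0.312) = 62% | Φ(−0.208) = 42% |
| 109 (121 × 0.9) | 0.0601 | 1.663 | Φ(0.223) = 59% | Φ(−0.297) = 38% |

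**4. Power of a trial sized exactly by the formula.** Here the planned power is Φ(z_b), and power at 5% is Φ(1.44 + z_b − 1.96). The power term can be read in three ways:

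| Reading | z_b | Power at 15% | Power at 5% |
|---|---|---|---|
| Stated value | 0.75 | 77% | Φ(0.23) = 59% |
| The words giving 75% | 0.674 | 75% | Φ(0.154) = 56% |
| Label taken as beta = 0.15 | 1.036 | 85% | Φ(0.516) = 70% |

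Taken literally, the label z_0.15/2 would be 1.44 again, which is not the value given. With z_b = 0.75, moving to 5% raises the required n by (2.71/2.19)² = 1.53, from about 189 to about 290 per arm.

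**5. What 121 per arm can detect at 5%.** For 22% v 38%, p = 0.30, SE = √(0.42/121) = 0.0589, and power = Φ(0.16/0.0589 − 1.96) = 77.5%. For 22% v 38.5% it is 79.8%.

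**The case against.** Several objections have weight.

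- **A reader might infer that the trial's power falls from 77% to 59%, whatever the sample size.** The documents do not support this. That drop belongs to a trial of exactly the size the formula returns, about 189 per arm, and to one of three conflicting readings of the power term. The article nowhere states 77%. For the 121 per arm planned, the figures are 62% and 42%.
- **The formula is not visible and 242 is not reproduced.** This stands. The per-arm sizes and powers assume the standard two-proportion form. The conflict between 15% and 5% does not depend on it, since both levels are stated outright.
- **The primary outcomes are not proportions.** Table 1 lists changes in knowledge, attitude and practice scores compared by t test, and the article does not say what 32% and 22% measure. So 42% is not the power for any named primary outcome; it describes the sizing calculation only.
- **A reader might infer that the type I error is inflated.** It is not, through this mismatch: the decision rule is a conventional 5%. The damage is to the claimed power.
- **A separate analysis plan or the full protocol may settle it.** The point is not an omission. Both levels stand in this article, and no later document can make 1.44 the right input for a two-sided 5% test.

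**Conclusion.** The point holds as a contradiction between the two sections: the sample size was derived at a two-sided 15% level and the results will be judged at 5%. For a 32% v 22% contrast with 121 pairs per arm, the mismatch takes power from about 62% to about 42%; with 109 per arm it is about 38% at 5%. A true difference of the assumed size would then be missed more often than found.

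These figures rest on the standard two-proportion approximation and on independent caregivers. Any positive correlation within the 10 clusters would lower them further. They do not carry over to the continuous scores. The power term is internally inconsistent, so the power originally intended can only be given as a range (75% to 85%, falling to 56% to 70% for a trial sized exactly by the formula).

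**What to change.** Keep P<.05 and two-sided 95% confidence intervals. In Sample Size Determination:

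1. Disclose that 242 was derived with a two-sided 15% level. Do not simply overwrite 1.44 with 1.96 beside an unchanged 242, since that would describe a calculation that was never done.
2. State beside it what 121 per arm delivers at two-sided 5%: about 42% power for 32% v 22% (about 38% with 109 per arm), or a detectable contrast of about 22% v 38% at 77–80% power.
3. Label these figures as before clustering and as describing a binary contrast, not the continuous knowledge, attitude and practice scores.
4. Say which power was intended and show how 242 was obtained.

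In the Data Analysis Plan, add that non-significant results will be reported with their confidence intervals and not read as absence of effect.

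The communities and pairs were already selected in February 2020, and no further enrolment or data collection is proposed. The cost is a short correction to the text and a less favourable stated power.

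### The trial is sized at a two-sided alpha of 0.15 but tested at 0.05, and the printed inputs do not lead to 242, so the implied power is not delivered

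*Protocol article*

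**What the plan says.** Sample Size Determination uses a formula for comparing two groups to obtain a minimum sample size. The inputs given are:

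- alpha term, then beta term: "z*_0.15/2_ = 1.44 (from *z* score table), Zβ/2 = z_0.15/2_ = 0.75 (from *z* score table at 75" per cent
- proportions: "P_1_= 0.32, P_2_ = 0.22"
- allowance for loss: "Considering the 10% nonresponse rate, the sample size (n) was adjusted to 242"

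The Abstract (Methods) shows that 242 is the total over both arms: "The intervention and control arms will each comprise 5 clusters with 121 child–caregiver pairs". Step 2 of Intervention Development agrees, with 121 caregivers in the intervention arm.

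The Data Analysis Plan fixes the test level: "The significance level will be set at a *P* value <.05". It also calls for two-sided 95% confidence intervals.

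Table 1 lists the three primary outcomes (caregiver knowledge, attitudes and practices) as continuous change scores compared by t test.

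**The concern.** Four things do not fit together.

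1. The trial is sized at one significance level and analysed at another, and nothing in the document reconciles them. This is not a slip of one digit, because the label 0.15/2 and the value 1.44 agree.
2. The same symbol, z at 0.15/2, equals 1.44 in the alpha term and 0.75 in the beta term. The intended power could be 75%, 77% or 85%.
3. The printed inputs do not appear to produce 242.
4. The sizing rests on an unnamed proportion, while the primary outcomes are mean score changes.

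The figure 242 is presented as the minimum for the planned comparison. If it falls well short at the level the trial will use, a reader who relies on that statement could take a non-significant result as evidence that the intervention does not work, when the trial had little chance of showing the effect assumed. Type I error is not affected, since testing is at 0.05.

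**Working it through.** **Inputs.** From Sample Size Determination: z for alpha 1.44, z for beta 0.75, P1 = 0.32, P2 = 0.22, so d = 0.10 and the mean proportion is 0.27; nonresponse 10%. From the Abstract: 121 per arm in 5 clusters. From the Data Analysis Plan: two-sided alpha 0.05, z = 1.96.

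**The z values.**
- The two-sided 15% critical value is 1.4395, so 1.44 is alpha = 0.15.
- The 75th normal percentile is 0.674. A z of 0.75 corresponds to 77.3%. If 0.15 were meant as beta (85% power), z would be 1.036.

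**Attempt to reproduce 242.** Per arm, n = (z_alpha + z_beta)² × V / d².
- (1.44 + 0.75)² = 4.7961.
- Unpooled V = 0.32 × 0.68 + 0.22 × 0.78 = 0.3892, so n = 4.7961 × 0.3892 / 0.01 = 186.7 per arm.
- Pooled V = 2 × 0.27 × 0.73 = 0.3942, so n = 189.1 per arm.
- Total: 373 to 378. With 10% nonresponse: 411 to 416 (× 1.1) or 415 to 420 (÷ 0.9).

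The plan has 242. Other readings tried:

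| Reading | Result |
|---|---|
| z_beta = 0.674 (exact 75%) | 176 per arm, 352 total, 392 after loss |
| Per-arm 189 taken as the total | 208 to 210 after loss |
| One-sided alpha 0.15, 75% or 77.3% power | 230 or 252 total; 256 or 280 after loss |
| Continuity correction, z_beta = 0.75 | 208 per arm, 232 per arm after loss |
| Mean proportion as literally printed, 0.32 + 0.22/2 = 0.43 | 235 per arm, 259 after × 1.1 |
| z_beta = 1.04 (85% power), pooled V | (2.48)² × 0.3942 / 0.01 = 242.4 per arm |

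Only the last row lands on 242. It is a per-arm figure, before nonresponse, and uses a z value that is not printed. A per-arm number may have been used as a total, but this cannot be confirmed.

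**Power of the planned size for 32% versus 22%, pairs treated as independent.** 242/1.1 = 220, so 110 per arm respond; 121 per arm is the figure without loss.
- 110 per arm: SE = √(0.3892/110) = 0.0595; 0.10/SE = 1.68. Power = Φ(1.68 − 1.96) = 0.39 at alpha 0.05 and Φ(1.68 − 1.44) = 0.60 at alpha 0.15.
- 121 per arm: SE = 0.0567; 0.10/SE = 1.76. Power = 0.42 at alpha 0.05 and 0.63 at alpha 0.15.
- A pooled variance under the null lowers these by half a percentage point or less.

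**Size needed at alpha 0.05 with the same beta term.** (1.96 + 0.75)² = 7.3441. Times 0.3892/0.01 this gives 286 per arm; times 0.3942/0.01, 290 per arm.

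**Clustering.** No design effect is among the printed inputs, and the intracluster correlation (ICC) is not given. With 121/5 = 24.2 pairs per cluster, the design effect is 1 + 23.2 × ICC. Assuming ICC = 0.01, 0.02 and 0.05, it is 1.23, 1.46 and 2.16, and power for 121 per arm at alpha 0.05 falls to about 35%, 30% and 22%.

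**What 121 per arm can detect on a continuous score**, in SD units of the change score, at 80% power and alpha 0.05, is (1.96 + 0.84) × √(2 × design effect / 121): 0.36 with no clustering, and 0.40, 0.44 and 0.53 at the three assumed ICCs. With 10 clusters a t reference on 8 degrees of freedom is more realistic (2.306 + 0.889 in place of 2.80). It gives 0.46, 0.50 and 0.60 at the same ICCs.

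**The case against.** The strongest reply is that the formula and the unadjusted n are missing from the text as extracted, so nobody can say that the protocol's own formula fails to give 242. That stands as a limit: non-reproduction is shown against the usual two-proportion formulas, not the printed one. It does not touch the conflict between 0.15 and 0.05 or the double value of one symbol, both of which are plain in the text.

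Second, the document never states a planned power outright; 77% is read off z = 0.75. That is fair, but the shortfall holds whether the target was 75%, 77% or 85%.

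Third, the power figures describe an unnamed proportion and not the primary outcomes. That also stands. The protocol does classify each knowledge measure as adequate or inadequate before combining them, and the Abstract names logistic models, so a proportion is not wholly foreign to the plan. Table 1 nonetheless makes the primary outcomes continuous. No SD or mean difference is given, so power for them cannot be calculated, and 242 cannot be called their minimum.

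Fourth, the planned 95% intervals would show the imprecision of a null result. They would help a careful reader, but they do not correct the stated basis of the sample size.

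**Conclusion.** The concern holds. The alpha used for sizing (0.15) contradicts the alpha used for testing (0.05), the beta term is internally inconsistent, and no standard reading of the printed inputs gives 242 as a total. For 32% versus 22%, power at alpha 0.05 is 39 to 42%, against the 75 to 85% that the beta term could mean; at alpha 0.15 it is still only 60 to 63%. Keeping the beta term of 0.75 at alpha 0.05 would take 286 to 290 per arm. These figures assume 1:1 allocation, independent pairs and a normal approximation; any positive ICC makes them worse. They apply to the stated proportions only.

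**What to change.** Enrolment is fixed: the Results section reports 242 pairs in 10 communities already selected. The change is therefore to the paragraph, not to the trial.

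- Restate Sample Size Determination at two-sided alpha 0.05, in line with the Data Analysis Plan. Say openly that the trial was originally sized with z = 1.44, so the history is not lost.
- Remove the claim that 242 is the calculated minimum.
- State one power, with the z value that belongs to it, and correct the beta notation.
- State what 10 clusters and 242 pairs deliver for the actual primary outcomes: the smallest detectable difference in each score, in SD units, at 80% power. Include the design effect over a stated range of assumed ICC, since the document gives none. At the ICCs assumed above (0.01 to 0.05) this is roughly 0.40 to 0.53 SD by the normal approximation, or 0.46 to 0.60 SD with 8 degrees of freedom, before nonresponse.
- If the 32% versus 22% comparison is kept, name the outcome and give its power at alpha 0.05.

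The cost is one rewritten paragraph and a less favourable statement of power. No participants are added and the analysis does not change.

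### The power term in the sample size calculation is wrong: one symbol carries two values, beta is halved, and 0.75 is not the normal quantile at 75%

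*Protocol article*

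**What the plan says.** All inputs are in the Sample Size Determination section of the protocol article.

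- Alpha term: "z*_0.15/2_ = 1.44 (from *z* score table"), which is the value for a two-sided alpha of 0.15.
- Power term, in the same sentence: "Zβ/2 = z_0.15/2_ = 0.75 (from *z* score table at 75"%).
- Proportions: "P_1_= 0.32, P_2_ = 0.22".
- Pooled prevalence: "pooled prevalence (prevalence in intervention group [P1] + prevalence in control group [P2]/2").
- Result: "Considering the 10% nonresponse rate, the sample size (n) was adjusted to 242".

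The Abstract (Methods) gives the split: "The intervention and control arms will each comprise 5 clusters with 121 child–caregiver pairs". The Data Analysis Plan tests at a different level from the one used for sizing: "The significance level will be set at a *P* value <.05". No section states a target power in words.

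**The concern.** Three things are wrong in the one line that fixes the power.

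1. z_0.15/2 is a single number. It cannot be 1.44 for alpha and 0.75 for beta.
2. Beta is divided by two. In a two-sided comparison of two groups only alpha is split between the tails; the power term is z_beta.
3. The table value at 75% is not 0.75. The entry may be the probability itself used as a z value, but the text does not confirm that.

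This sentence is the only source for the planned type II error. A reader who wants to know what the trial was designed to detect, and with what chance, has to guess which element of the line to believe.

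**Working it through.** **Quantiles.** z(0.925) = 1.4395, so 1.44 is right for alpha = 0.15 two-sided. z(0.75) = 0.674. Φ(0.75) = 0.773. z(0.85) = 1.036.

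**What each element of the line implies.**

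| Element taken at face value | z | Power |
|---|---|---|
| Label, 75% | 0.674 | 75% |
| Number entered, 0.75 | 0.75 | 77.3% |
| Subscript, beta = 0.15 | 1.036 | 85% |
| Subscript, beta/2 = 0.075 | 1.44 | 92.5% |

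**Reproducing 242.** The printed formula is not visible, so its form is an assumption. Two routes land close to 242 after nonresponse. Both read the pooled prevalence as printed, without a bracket around the sum: 0.32 + 0.22/2 = 0.43.

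- Pooled and unpooled variance form, z = 0.75: n = [1.44·√(2·0.43·0.57) + 0.75·√(0.32·0.68 + 0.22·0.78)]² / 0.10² = (1.0082 + 0.4679)² / 0.01 = 217.9. Then 217.9/0.9 = 242.1.
- Simple pooled form, z = 0.674: n = 2·0.43·0.57·(1.44 + 0.674)² / 0.10² = 219.1. Then 219.1/0.9 = 243.4, or 219.1 × 1.1 = 241.0.

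In the first form with 0.43, z = 1.036 gives 304 and z = 1.44 gives 404 after nonresponse. In the second they give 334 and 452. None of these matches 242.

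**With the usual pooled prevalence**, (0.32 + 0.22)/2 = 0.27, and the simple pooled form, n per arm = (1.44 + z_β)² × 2·0.27·0.73 / 0.10² = (1.44 + z_β)² × 39.42:

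- z = 0.674: 2.114² × 39.42 = 176.2 before nonresponse; 195.7 after dividing by 0.9.
- z = 0.75: 2.19² × 39.42 = 189.1 before nonresponse; 210.1 after.

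**Power of 121 per arm for 0.32 against 0.22, ignoring clustering.** Power = Φ{[0.10·√n − z_α/2·√(2·0.27·0.73)] / √(0.32·0.68 + 0.22·0.78)}.

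- Alpha 0.05: (1.100 − 1.960 × 0.6279) / 0.6239 = −0.209, so power is 41.7%.
- Alpha 0.15: (1.100 − 1.4395 × 0.6279) / 0.6239 = 0.314, so power is 62.3%.
- If 10% are lost, about 109 per arm remain, and power is 38% and 59%.

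**Clustering.** The document gives no intracluster correlation (ICC), so the values below are assumptions. The mean cluster size is 121/5 = 24.2, and the design effect is 1 + 23.2 × ICC.

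| Assumed ICC | Design effect | Power, alpha 0.05 | Power, alpha 0.15 |
|---|---|---|---|
| 0.01 | 1.232 | 35% | 56% |
| 0.02 | 1.464 | 30% | 50% |
| 0.05 | 2.16 | 22% | 40% |

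**The case against.** The best defence is that the intention can still be seen. The number and the label agree to within a little over two percentage points of power, and they differ by only 13 per arm (176 against 189). The 85% and 92.5% readings rest on the subscript alone, which the number and the label both contradict. The two back-calculations above also point to 0.75 or 0.674. This argument largely stands, and it limits the point in three ways.

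- A reader might infer that the planned power is undefined. The text does not support that: about 75 to 77% is the likeliest intention. It has to be inferred, though, because 242 can be reached at either value. The value z = 1.036 with pooled prevalence 0.27 also gives 241.7, but before any nonresponse allowance, whereas the document describes 242 as the figure after it.
- A reader might set all four readings side by side and report needs from 176 to 327 per arm, a 1.9-fold range. The upper end requires setting aside both the number and the label, so it is not a fair measure of the ambiguity.
- A reader might blame this error for the gap between 176 or 189 and 121 per arm. The gap is there under the likeliest readings too. It comes mainly from a per-group result apparently being used as the total for both arms, which is a separate fault.

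It can also be said that 242 pairs were already selected in February 2020 and that a null result will be judged mainly by its confidence interval. Both are fair. They lower the stakes, but they do not make the line correct.

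**Conclusion.** The point holds as an error of notation and quantile in the only statement of power the document contains. The alpha value is correct for its label; the power value is not correct for any of its labels. The likely target was 75 to 77%. The power that 121 per arm gives on the plan's own proportions is lower than any reading of the line: about 62% at the sizing alpha and about 42% at the level the analysis will use, both before clustering.

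The per-arm numbers rest on the standard two-proportion formula with pooled prevalence 0.27, because the printed formula cannot be seen. The clustered figures rest on assumed correlations. Other problems in the same calculation weigh more: the pooled prevalence as printed, the apparent use of a per-group n as a total, alpha 0.15 for sizing against 0.05 for analysis, and no visible allowance for 10 clusters. Repairing the power term alone therefore does not make 242 a valid sample size.

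**What to change.** In Sample Size Determination:

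1. Replace the halved-beta term with z_β.
2. Name one target power and use its quantile (0.674 for 75%, 0.842 for 80%, 1.036 for 85%).
3. Recompute, showing the formula and saying whether n is per arm or in total.
4. State the power that 121 per arm gives at the analysis alpha of 0.05 for 0.32 against 0.22 (about 42% before clustering). The figure at the sizing alpha of 0.15 (about 62%) may stand beside it, if labelled as such.
5. Say that clustering over 10 clusters lowers both, and give the intracluster correlation assumed.

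The alpha and the clustering basis must be named, because the power of 121 per arm is ambiguous without them. The cost is one corrected line and a short statement of power. No added enrolment or other change to the conduct of the trial is needed.
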